### Study intervention

After the patients have meet all inclusion/exclusion criteria during visit 1 (preliminary/baseline), they will receive an intraarticular injection of CCM (2 ml, General Therapeutics LLC, Cleveland Heights, OH, USA) formulation via anterolateral approach by the site principal investigator (PI) utilizing ultrasound guidance per PI’s standard institutional protocol during visit 2.1 (injection visit/procedure).

### Assessment points

The assessments for the study period will begin at visit 1 (preliminary/baseline), where patients will be screened for the inclusion/exclusion criteria and asked to sign the informed consent form. Once enrolled, the demographic information, medical history, medication history, and vitals will be collected. A baseline physical exam (PE) that includes knee ligament laxity and active/passive range of motion evaluation will be performed. Baseline plain radiography (weight bearing anteroposterior, lateral with 30° of knee flexion, Merchant and Rosenberg views) and MRI imaging (including T2 imaging and institutional standard protocol) will be performed for OA grading using the KL scale and Magnetic Resonance Observation of Cartilage repair Tissue (MOCART) score, respectively. Baseline case report forms (CRFs) including NPRS, KOOS Jr., PROMIS, Neuro-QoL Short Form v1.0, Lower extremity function-Mobility, PROMIS Short Form V2.0 - Physical Function 10a and 10b, and patient satisfaction/survey (SF-36 and Single assessment Numeric Evaluation (SANE)) will be collected. Additionally, a comprehensive metabolic profile (CMP), creatinine (Cr), erythrocyte sedimentation rate (ESR), T, B, and NK cell lymphocytes subsets, and serum IgG, IgA, IgM, and IgE levels will be collected. The vitals will be recorded followed by administration of injection by the site PI on visit 2.1. During visit 2.2 (immediately after injection follow-up + 15 min after injection), the vitals and NPRS will be recorded. Visits 3 (24 h follow-up ± 2 h) and 4 (48 h follow-up ±2 h) will be completed via phone interview, and NPRS will be collected. On visit 5 (1 week follow-up ±1 day), a PE will be performed and specific CRFs (NPRS, KOOS Jr., PROMIS, 5 point Likert scale and SANE) as well as a comprehensive metabolic profile (CMP), creatinine (Cr), erythrocyte sedimentation rate (ESR), T, B, and NK cell lymphocytes subsets, and serum IgG, IgA, IgM, and IgE levels will be collected. The exact same process will take place through visits 6 (6 week follow-up ± 3 days), 7 (3 month follow-up ± 7 days), and 8 (6 month follow-up ± 14 days) with a plain radiograph at each visit. SF-36 will also be collected at visits 7 and 8. At visit 9 (12 month follow-up ± 21 days), the participants will undergo the aforementioned processes with an MRI for MOCART grading. At visit 10 (18 month follow-up ± 28 days), the participants will undergo a PE, plain radiography, and CRFs (NPRS, KOOS Jr., PROMIS, 5 point Likert Scale, SANE and SF-36). At visit 11 (24 month follow-up ± 28 days), the participants will undergo the aforesaid processes with an MRI for MOCART grading. An empirical grading form evaluating six distinct articular elements namely, cartilage, osteophytes, subchondral sclerosis, bone marrow lesions, joint effusion, and synovitis, involved in the pathoanatomy of knee osteoarthritis using MRI will also be evaluated at baseline and at 12- and 24-month follow-up visits [36]. Participants may report any adverse events or changes in medications at any point during the study. Unscheduled visits may occur at any time for possible study-related adverse events.

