#### Exclusion criteria

In addition to the inclusion criteria, patients must not meet any of the following exclusion criteria:
Taken any pain medications, including NSAIDS, within 15 days prior to the study injection date.Use of anticoagulants or history of the regular use of anticoagulantsHistory of addiction to dependency producing medications or substance abuse, including alcohol or illicit drugsMechanical knee symptoms consistent with extensive intraarticular pathology not amenable to injection therapy alone, including clinical or imaging evidence of anterior cruciate ligament, posterior cruciate ligament, medial collateral ligament, lateral collateral ligament, or meniscal pathologyUndergone an intraarticular injection of any drug or device including but not limited to corticosteroid, platelet rich plasma or viscosupplementation in the index knee within the last 3 monthsHistory of any type of surgery in the index kneeRecent (within 3 months) history of traumatic injuryPlanned elective knee surgery during the duration of the studyHistory of organ or hematologic transplantationHistory of rheumatoid arthritis or other autoimmune disordersHistory of immunosuppressive medication/treatment or cancer diagnosis within the last 5 yearsCurrent knee infection or history of using antibiotics for a knee infection within the last 3 monthsParticipation within another clinical study or received treatment with any investigational product within 30 days of enrollmentCurrently pregnant, as determined by urine testingBreastfeeding, or desires pregnancy during the course of the studyContraindications to plain radiography or MRI imagingDiagnosis of progressive neurological diseaseDiagnosis of an active psychological or psychiatric disorderPain within other areas and/or medical conditions that could interfere with pain reporting, study procedures, and/or confound evaluation of the studyUnresolved major issues of secondary gain (e.g., social, financial, or legal)

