#### Secondary endpoints

To assess the changes if any in patient-reported outcome measures, NPRS, PROMIS, and KOOS Jr., from baseline to different follow-up time points.To assess cartilage formation via MOCART at 2 years time point and compare it from baseline.To assess patient satisfaction.

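### Baseline NPRS is collected at the same visit that selects patients on NPRS, and the text names no score between selection and injection, so NPRS change carries regression to the mean

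*Protocol article*

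**What the plan says.** The Inclusion criteria of the protocol article require an average knee pain of at least 6 on the NPRS, with no recall window given. Under Assessment points, screening and baseline are one visit: "The assessments for the study period will begin at visit 1 (preliminary/baseline), where patients will be screened for the inclusion/exclusion criteria". Study intervention likewise has all criteria met at visit 1, before the injection visit. The baseline forms belong to that visit too: "Baseline case report forms (CRFs) including NPRS, KOOS Jr., PROMIS" and others.

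For the injection day the text reads: "The vitals will be recorded followed by administration of injection by the site PI on visit 2.1". The next NPRS comes after dosing: "During visit 2.2 (immediately after injection follow-up + 15 min after injection), the vitals and NPRS will be recorded".

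The secondary endpoint depends on the baseline value: "To assess the changes if any in patient-reported outcome measures, NPRS, PROMIS, and KOOS Jr., from baseline to different follow-up time points". The Background states a null hypothesis of no difference between baseline and follow-up. The statistical section plans paired tests and a mixed model at P < 0.05. There is a single open-label arm of about 12 treated patients.

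The analgesic exclusion is dated from the injection, not from visit 1: "Taken any pain medications, including NSAIDS, within 15 days prior to the study injection date". The article gives no interval between visits 1 and 2.1.

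**The concern.** A patient's NPRS on a given day is usual pain plus day-to-day fluctuation. Requiring a high value at visit 1 favours patients who were having a worse day than usual. Their later scores tend to fall back even if nothing has changed. If the change score starts from the selecting visit, that fall is counted as improvement. A randomised comparison would cancel it between arms; here nothing does.

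The bias has a known direction, in favour of the product, and it applies at each of the ten NPRS times after the injection (visits 2.2 to 11). It matters beyond this study because the Discussion says the results will lay the foundation for a larger randomised trial. An inflated NPRS change could be carried into that trial's assumed effect.

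Medication state is a second and less certain issue. Because the restriction counts back from the injection, a visit 1 score could be given while analgesics are still being taken, and later scores without them.

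**Working it through.** The article gives no effect size, SD or power, so there is no figure of its own to reproduce.

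**Inputs from the article:** entry at NPRS 6 or more; selection and baseline both at visit 1; 12 treated patients; paired t test among the planned tests; P < 0.05 (two-sided assumed).

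**Assumptions, none given in the article:** SD 2; unselected mean NPRS 5, 6 or 7; test-retest correlation r from 0.5 to 0.9; no true change.

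**Step 1, formula.** With threshold c = (cut − mean)/SD and λ = φ(c)/(1 − Φ(c)), the expected spurious fall is (1 − r) × SD × λ. With the cut at 6:

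- Mean 6, r 0.7: c = 0, λ = 0.798, fall = 0.3 × 2 × 0.798 = 0.48 points.
- Mean 5, r 0.5: c = 0.5, λ = 1.14, fall = 0.5 × 2 × 1.14 = 1.14 points.
- Mean 7, r 0.9: c = −0.5, λ = 0.51, fall = 0.1 × 2 × 0.51 = 0.10 points.

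NPRS is scored in whole numbers, so the effective cut is nearer 5.5. The same three cases then give 0.39, 0.96 and 0.08. Letting SD vary from 1.5 to 2.5 with the cut at 6 widens the range to 0.06 to 1.34.

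**Step 2, simulation.** Scores were rounded and limited to 0–10, patients were selected at 6 or more and grouped in twelves. Each group was tested with a two-sided paired t test at 0.05, about 20,000 trials per row. The last column counts significant results in the direction of improvement (nominal 2.5%).

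| Unselected mean | r | Mean change with no effect | Declared improved |
|---|---|---|---|
| 5 | 0.5 | −1.00 | 40.1% |
| 5 | 0.7 | −0.62 | 25.1% |
| 5 | 0.8 | −0.42 | 18.2% |
| 5 | 0.9 | −0.23 | 10.9% |
| 6 | 0.5 | −0.68 | 20.2% |
| 6 | 0.7 | −0.41 | 13.4% |
| 6 | 0.8 | −0.28 | 10.0% |
| 6 | 0.9 | −0.16 | 6.9% |
| 7 | 0.5 | −0.40 | 9.7% |
| 7 | 0.7 | −0.25 | 7.5% |
| 7 | 0.8 | −0.17 | 5.9% |
| 7 | 0.9 | −0.09 | 4.6% |

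**Step 3, a separate pre-injection baseline.** If its error is independent of the visit 1 error, the mean change is 0.0 and the rate is 2.3% to 2.5% in every row. If the two errors correlate at ρ, the remaining bias is ρ times the Step 1 value. At ρ = 0.5, the case with mean 6 and r 0.7 keeps 0.5 × 0.48 = 0.24 points, about half.

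**Step 4, multiplicity.** As an illustration, Bonferroni over the ten post-injection times tests each at 0.05/10 = 0.005, or 0.25% in the direction of improvement. For means 5 to 6 and r 0.5 to 0.8, the false rate per comparison is about 1.5% to 11%. It is lower than in the table but still above nominal, and the mean shift is unchanged.

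**The case against.** **The same score?** A reader might infer that the selecting score and the baseline score are one and the same. The text fixes the same visit, not the same entry: the criterion is an average, and the baseline forms are listed after enrolment. A true average would be more reliable, which moves toward the lower rows of the table. A separate current-pain rating would not be cut off exactly at 6. This stands as a limit on size. It does not remove the bias, because two ratings at one visit share most of their transient error.

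**Every outcome?** A reader might also extend the point to all change scores. Selection is on NPRS. KOOS Jr. and PROMIS are affected only through their correlation with it, and no effect is shown for MOCART.

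**Silence of the text.** The SPIRIT schedule in Fig. 2 is not shown and could list an NPRS at visit 2.1; it would then have to be reconciled with the text. The statistical section also lists baseline and visit 1 as separate time levels, so the analysis baseline is not cleanly fixed. Still, the visit-by-visit text names NPRS at 15 minutes, 24 hours and 48 hours and none before the injection.

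**The planned analysis.** The largest rates come from one uncorrected paired test, whereas corrected post hoc tests and a mixed model are planned. This is fair as to the rates. A mixed-model contrast with the same baseline carries the same shift.

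**Medication state.** Nothing says that visit 1 scores are given on analgesics. If they were, later scores off medication could be higher, which would oppose regression to the mean. This is a possibility of unknown direction and no more.

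**Conclusion.** The concern holds for NPRS. Selection and baseline share visit 1, no score is named between selection and injection, and there is no control arm, so regression to the mean biases NPRS change toward improvement. The bias is about 0.1 to 1.0 points, and the false-improvement rate about 5% to 40% for an uncorrected paired t test with 12 patients. Both ranges rest on the assumed SD of 2, means of 5 to 7 and correlations of 0.5 to 0.9, and on modelling selection and baseline as one score. With a high mean and high reliability the effect is small.

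A reader might infer that the study cannot proceed without this change. The article does not support that. It describes a preliminary feasibility and safety study, the primary endpoint is safety, and NPRS change is one of several secondary endpoints. The change is a cheap improvement that should be made, and it has to be made before dosing because the missing score cannot be recovered afterwards.

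**What to change.** Record NPRS at visit 2.1 before the injection. Define that value as the baseline for all NPRS change analyses, and use the visit 1 score for eligibility only. Make the statistical section's list of time points agree with this definition.

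The cost is one 0–10 question at a visit the patient already attends, and a slightly smaller reported improvement. The new baseline would also be scored on the date from which the analgesic exclusion is counted, which addresses the possible medication mismatch for NPRS.

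The limits should be stated when the results are reported. The selection bias disappears fully only if errors at visits 1 and 2.1 are independent; about half remains at an error correlation of 0.5. Placebo response and natural course stay mixed with any treatment effect in a single open-label arm.

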
### Endpoints

#### Primary endpoint

To determine the safety of intraarticular administered CCM, including monitoring for adverse injection reactions including immunogenic or allergic responses or infection.

#### Secondary endpoints

To assess the changes if any in patient-reported outcome measures, NPRS, PROMIS, and KOOS Jr., from baseline to different follow-up time points.To assess cartilage formation via MOCART at 2 years time point and compare it from baseline.To assess patient satisfaction.

### Sample size and statistical analysis

Descriptive statistics will be computed for all study variables. Continuous variables will be described with measures of central tendency (mean, median) and dispersion (range, standard deviation). Categorical variables will be summarized as frequencies and percentages. Comparisons between categorical variables will be compared with the chi-Square test; continuous variables will be compared with Student’s *t* test or nonparametric equivalents. Paired continuous data will be assessed with a paired *t* test or Wilcoxon signed rank test, depending on distribution. Paired categorical data will be assessed with the McNemar’s test. For the longitudinal data, a mixed model repeated measures analysis will be used to examine the between subject factors and the within subject factor of time (baseline, visit 1, visit 2, etc.), as well as their interaction, on the outcome variables of interest. Post hoc tests with corrections for multiple comparisons will be run to determine where significance lies. *P* values < 0.05 will be considered statically significant.

### Data collection and handling

The PI will be responsible for the maintenance of source documents and records for a period of 7 years. Data will be transcribed on paper study CRFs, and the original data will be secured by the PI and made available to the sponsor and study monitors. All CRFs will be subject to initial inspection for omitted data, data inconsistencies, illegible data, and deviations by study monitors. All hard copies of CRFs and media will be stored in a secure location for 7 years.

The PI will be responsible for submitting data and reports as follows:
AEs: In an ongoing basis. This will be reported in the proper section of the CRF.SAEs: Report within 24 h of knowledge of event to sponsor and report to IRB within 5 days as per their regulations.Deviations, exceptions, violations of protocol: Report to sponsor within 5 days and report to IRB per their regulations.Protocol progress report: Provide a copy to sponsor and IRB as per regulations.Study closure report: Provide a copy to sponsor and IRB as per regulations.

### Quality control and assurance

All documents related to the study will be produced and maintained to ensure control and protection of patient’s privacy. The sponsor, study monitors, and representatives of regulatory authorities are permitted to access all study documents (e.g., protocol, CRFs, medical records/files) as needed. All attempts will be made to preserve patients’ privacy and confidentiality.

## Discussion

OA is one of the most common musculoskeletal conditions in the USA, affecting several joints and leading to pain, loss of function, and a decrease in quality of life [37]. This also leads to a substantial burden on the healthcare system [38]. The knee is the most frequently affected joint, and current efforts to mitigate knee OA are focused on decreasing pain, increasing function, and improving quality of life [38]. These current treatment options have limitations, as symptomatic treatment fails to address the underlying pathophysiological processes associated with OA or regenerate injured cartilage [38]. This is one of the several reasons why the field of regenerative medicine and interest in the use of biologics, including cell-free biologics, has increased so rapidly [27, 34, 37].

This clinical trial will be the first to evaluate the safety and efficacy of intraarticular cell-free stem cell-derived extract (CCM) in patients with Kellgren grade II or III knee OA. We anticipate that the intraarticular injection of CCM is safe, and participants will show an improvement in their pain, function, quality of life, and overall satisfaction. We also hypothesize that the cartilage formation over a period of 2 years compared to the baseline visit will improve. The positive outcomes from this trial will also lay the foundation for a large randomized, placebo-controlled, multi-center trial of intraarticular CCM for symptomatic knee OA.

## Data Availability

The datasets used and/or analyzed during the future study will be available from the corresponding author on reasonable request.

## Abbreviations

CCM: Cell-free stem cell-derived extract
CKs: Cytokines
CRFs: Case report forms
EVs: Extracellular vesicles
GFs: Growth factors
hPESCs: Human progenitor endothelial stem cells
KL: Kellgren-Lawrence scale
KOOS Jr.: Knee Injury and Osteoarthritis Outcome Score
MOCART: Magnetic Resonance Observation of Cartilage Repair Tissue
MSCs: Mesenchymal stem cells
NPRS: Numeric pain rating scale
OA: Osteoarthritis
PI: Principal investigator
SANE: Single Assessment Numeric Evaluation
SPIRIT: Standard Protocol Items-Recommendations for Intervention Trials
